# Ropivacaine 75 mg versus placebo in perineal infiltration for analgesic efficacy at mid- and long-term for episiotomy repair in postpartum women – the ROPISIO study: a two-center, randomized, double-blind, placebo-controlled trials

**DOI:** 10.1186/s13063-020-04423-x

**Published:** 2020-06-12

**Keywords:** Perineal pain, Episiotomy, Ropivacaine, Local infiltration

## Abstract

**Background:**

Perineal pain due to episiotomy is commonly reported and can be severe enough to disturb the mother–infant dyad during the postpartum period. Its incidence at day 7 postpartum varies from 63% to 74%. Recent studies have investigated the analgesic efficacy of perineal infiltration of ropivacaine after episiotomy but have only focused on the immediate postpartum period (at 24 and 48 h after birth). Large, adequately powered, multicenter, randomized controlled trials are required to evaluate the impact of ropivacaine infiltration on perineal pain and mid- and long-term quality of life before the widespread use of ropivacaine to prevent perineal pain after episiotomy can be recommended.

**Methods/design:**

The ROPISIO study is a two-center, randomized, double-blind, placebo-controlled trial being conducted in La Roche sur Yon and Nantes, France. It will involve 272 women with vaginal singleton delivery and mediolateral episiotomy at term (≥ 37 weeks). Perineal infiltration (ropivacaine 75 mg or placebo) will be administrated just after vaginal birth and before episiotomy repair. The primary outcome will be the analgesic efficacy at day 7 postpartum (midterm), defined by the Numeric Pain Rating Scale (NPRS) strictly superior to 3/10 on the perineal repair area. Secondary outcomes will be the analgesic efficacy (NPRS) and the impact of pain on daily behavior, on the quality of life (36-item Short Form Health Survey), on the occurrence of symptoms of postpartum depression (Edinburgh Postnatal Depression Scale), and on sexual health (Female Sexual Function Index) at 3 and 6 months (long-term) using validated online questionnaires. This study will have 90% power to show approximately 30% relative risk reduction in the incidence of perineal pain at day 7, from 70.0% to 50.0%.

**Discussion:**

Ropivacaine is a promising candidate drug, inexpensive, and easy to administer, and it would be suitable to include in the routine management of deliveries in labor ward. This study will investigate if perineal ropivacaine infiltration just after birth can reduce mid- and long-term postpartum pain and increase quality of life in women with mediolateral episiotomy.

**Trial registration:**

ClinicalTrials.gov, NCT03084549. Registered on 14 April 2017.

## Background

Episiotomy is a surgical enlargement of the vaginal orifice performed with scissors and requires sutures to be repaired [1]. The midwife or the obstetrician can perform an episiotomy to facilitate childbirth in case of severe fetal heart rate anomaly, and it is occasionally conducted to prevent obstetric anal sphincter injury in vaginal delivery [2]. Considering all maternal consequences of episiotomy, its routine use has been questioned, and restrictive episiotomy policies are recommended by clinical practice guidelines [3]. Despite this restrictive policy, episiotomy is still a common surgical procedure [4].

Perineal pain is a common consequence of episiotomy and affects up to 97% of women on day 1 postpartum [5, 6] and up to 70% of women at days 7 to 10 postpartum [7–9], and it may persist until at least 5 months postpartum [10, 11]. Pain after the perineal wound (apart from episiotomy) is also reported but less studied because of the high variability of the localization and the depth of the tear. Postpartum perineal pain may have a negative maternal impact, can affect the quality of life of the mother, and may be severe enough to disturb the postpartum period and the mother–infant dyad [5, 6]. Symptoms of postpartum depression affect 10–15% of women [12, 13]. An association between persistent perineal pain and symptoms of postpartum depression has been identified by several studies [14, 15]. After adjustment for covariates, an increased risk for depression was shown at 4–6 weeks and 6 months among women who had perineal pain compared with those without perineal pain [16]. In this prospective study, pain at 3–5 days postpartum was a predictor of symptoms of postpartum depression at 3 months [16]. Moreover, a dyspareunia rate of approximately 25% was observed in women who had an episiotomy [17]. Sexual disorders in women with postpartum perineal pain have previously been reported [10, 18, 19]. In addition, a clinical study showed that 12.8% of the women who underwent episiotomy presented with chronic perineal pain at 5 months, which was related to obstetric and postpartum factors (i.e., perineal pain in the first 48 h) [11].

Obstetric analgesia after a vaginal delivery received less attention than pain during labor or after a cesarean delivery. Epidural analgesia allows episiotomy to be performed without additional anesthesia. Therefore, local anesthetic injection at the time of the episiotomy may be necessary, even for women with epidural analgesia. Anesthetic perineal infiltration is the subcutaneous muscular aponeurotic space or serosal injection of analgesic drug next to the surgical site. Its effectiveness is based on the widest possible diffusion of the product and on the blocking of the most distal nerve endings [20]. The main property of local anesthetic drugs is to temporarily block pain message transmission from nociceptive terminations. Locally injected into an operative scar, the action of anesthetic drugs exceeds this framework. Local anesthetic drugs have an anti-inflammatory effect that limits self-maintenance of pain in peripheral lesions. Furthermore, clinical studies confirm that local anesthetic infiltration, even in a single postoperative injection, is beneficial over a period that exceeds the product’s persistence at the site of administration. Another prospective randomized study concerning groin hernia surgery showed that local anesthesia was superior to regional or general anesthesia in decreasing postoperative complications, duration of surgery and anesthesia, length of postoperative hospital stay, and time to normal activity [21]. For inguinal hernia repair, preoperative inguinal infiltration of ropivacaine provides benefits for patients in terms of faster recovery, less pain, better mobilization, and higher satisfaction throughout the first 7 days postoperatively [22]. For tonsillectomy under general anesthesia, preoperative infiltration of tonsils with bupivacaine showed that almost no constant pain occurred in the bupivacaine group at 5 days postoperatively compared with normal saline serum, and the difference in pain intensity was present even on the tenth postoperative day [23].

Ropivacaine is a drug already used in clinical practice for the treatment of acute pain in adults. For example, during childbirth (continuous or bolus epidural infusion), parietal infiltration or peripheral nerve blocks have been reported to be associated with a high rate of decreased pain [24]. Ropivacaine is an anesthetic with longer duration than lidocaine [25]. A complication of infiltration techniques is the systemic toxicity of local anesthetics. This results from large doses of anesthetic administration or from an injection into a space with important systemic resorption. In both cases, this can be prevented with knowledge of the products and injection sites and observing usual precautions when injecting a local anesthetic.

Three studies have already studied the analgesic efficacy of ropivacaine in perineal infiltration after episiotomy [26–28]. Gutton et al. [26] found a significant decrease of pain measured using a visual analogue scale (VAS) at 24 h in a cohort of 102 women in the ropivacaine group (3; 95% CI, 1.5 to 4) versus lidocaine group (4; 95% CI, 2 to 6) (*p* = 0.004). Moreover, the proportion of patients with a VAS ≤ 4 was significantly higher in the ropivacaine group (70.6% versus 43.1%; *p* = 0.009). These results remained at 48 h. In an unblinded study, Sillou et al. [28] compared the injection of ropivacaine in the margin of the episiotomy (*n* = 31) with the absence of infiltration (*n* = 31). The pain evaluated by NPRS was significantly lower in the ropivacaine group at hour 4 (H4) (1.9 ± 0.3 versus 3.6 ± 0.5; *p* = 0,006), H8 (3.3 ± 0.4 versus 5.2 ± 0.4; *p* = 0.003), H12 (2.8 ± 0.4 versus 5.2 ± 0.4; *p* = 0,0001), and H24 (2.6 ± 0.4 versus 4.3 ± 0.4; *p* = 0.006). However, in a cohort of 154 women, Schinkel et al. [27] compared the injection of ropivacaine versus lidocaine versus normal saline serum and did not find differences at 24 h in terms of time to first oral analgesic request (13.9 h versus 17.0 h versus 16.6 h; *p* = 0.104), proportion of patients who did not request oral analgesics (35% versus 54% versus 53%; *p* = 0.09), and VAS score (ropivacaine 16.8 ± 11.6; lidocaine 12.4 ± 9.7; saline 16.2 ± 11.5; *P* = 0.08). These studies focused on 24 and 48 h after childbirth, and no analysis of the mid- and long-term pain levels, dyspareunia, or depression occurrence was conducted. If the mother has less pain at midterm (7–10 days postpartum), it could increase mother–infant interaction and bonding.

Mediolateral episiotomies in the early and midterm postpartum period are associated with perineal pain. Both theoretical arguments and results of previous studies indicate that ropivacaine has promise in the prevention of perineal pain. Nevertheless, there are not enough well-conducted studies to reach any definitive conclusion. We therefore designed the present randomized controlled trial (Study of the Analgesic Effect of the Perineal Infiltration of Ropivacaine 0.75% versus Placebo in Post-episiotomy Perineal Pain [ROPISIO]). This study is a superiority study of ropivacaine 75 mg versus placebo in perineal infiltration for women receiving episiotomy. The primary endpoint is analgesic efficacy at day 7 (D7) postpartum (midterm) measured with the Numeric Pain Rating Scale (NPRS). The patients will be recruited at two centers.

## Methods/design

### Aim, design, and setting

The aim of this study is to compare the analgesic effect of a perineal infiltration of ropivacaine after vaginal delivery with mediolateral episiotomy versus placebo in a two-center, randomized, double-blind, placebo-controlled trial. The outcomes are the at short-term, midterm, and long-term impacts of perineal infiltration of ropivacaine 75 mg on perineal pain after vaginal birth and mediolateral episiotomy for medical indications on different symptoms. The specific outcomes are as follows:
Primary outcome: midterm perineal pain at day 7 postpartum measured with the NPRS strictly superior to 3/10 on the perineal repair areaSecondary outcomes:
Short-term postpartum perineal pain (at 12, 24, and 48 h) and long-term perineal pain (at 3 and 6 months) using the NPRSThe use of analgesic for perineal pain between H2 and H12, H12 and H24, H24 and H48, H48 and D7, and month 3 (M3) and M6 postpartumThe impact of pain on daily behavior with a scale of pain repercussions on daily behavior at D7, M3, and M6 postpartumThe type of persistent pain at D7, M3, and M6 postpartum with the simplified *Douleur Neuropathique* 4 (DN4) questionnaire at D7, M3, and M6The impact of perineal pain on the quality of life using the 36-item Short Form Health Survey (SF-36) at D7, M3, and M6 postpartumThe impact of perineal pain on the occurrence of symptoms of postpartum depression using the Edinburgh Postnatal Depression Scale (EPDS) at D7, M3, and M6 postpartumThe impact of perineal pain on female sexual health using the Female Sexual Function Index (FSFI) at D7, M3, and M6 postpartum

The ROPISIO study is a two-center, randomized, double-blind, placebo-controlled trial in two tertiary centers (one general hospital and one university hospital) designed to test the hypothesis that ropivacaine perineal infiltration after mediolateral episiotomy will reduce postpartum pain in the midterm and long term and increase quality of life. Figure 1 shows an adapted version of the Standard Protocol Items: Recommendations for Interventional Trials (SPIRIT) figure for the ROPISIO trial.

**Fig. 1 Fig1:**
[figure not shown]
Standard Protocol Items: Recommendations for Interventional Trials (SPIRIT) figure. The figure shows the phases of the trial and data collection time points. *DN4* Douleur Neuropathique 4, *EPDS* Edinburgh Postnatal Depression Scale, *FSFI* Female Sexual Function Index, *SF-36* 36-Item Short Form Health Survey

### Study population

Information on the trial will be provided to patients without planned cesarean section by obstetricians and midwives during the eighth month of pregnancy in La Roche sur Yon and Nantes, France, maternity hospitals. At the latest, this information will be given to women when they arrive in the delivery room. They will then confirm their participation and provide informed written consent before delivery. All randomized patients will be included in the full analysis set (intention-to-treat basis).

To be randomized, patients should fulfill all of the following inclusion criteria: (1) age ≥ 18 years, (2) age at birth ≥ 37 weeks of gestation, (3) spontaneous vaginal delivery or operative vaginal delivery, (4) singleton pregnancy, (5) mediolateral episiotomy, (6) delivery under epidural anesthesia, (7) patient can be followed up during the 6-month study, and (8) patient can understand the protocol.

Exclusion criteria are as follows: (1) known allergy to local anesthetics, (2) opioid dependence, (3) chronic pelvic pain before pregnancy, (4) women deprived of liberty (trusteeship, guardianship), (5) liver or kidney diseases, (6) acute porphyria, (7) elective cesarean section, (8) third- and fourth-degree perineal tears, (9) multiple pregnancy, and (10) poor understanding of French language.

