### Randomization

The randomization will be centralized and stratified by center and parity and will be performed according to a 1:1 ratio. The randomization will be performed by nonvarying size block. A computer-generated randomization list will be carried out by a statistician before the study begins. Once a woman has been included through the filing of an electronic case report form (eCRF) directly via the internet (Clinsights software; Glassbeam, Santa Clara, CA, USA), she will retain her randomization number (if it has been assigned to her) even if she withdraws from the study or refuses randomization afterward.

Women will be randomized after episiotomy and before the beginning of the suture to receive either 75 mg of ropivacaine (Fresenius Kabi, Sèvres, France; marketing authorization number 3400957740832 [2009, RCP rev. 08/09/2016]) in a 20-ml syringe (10 ml of ropivacaine 7.5 mg/ml and 10 ml of normal saline) or 20 ml of placebo (normal saline; Fresenius Kabi, Sèvres, France; marketing authorization number 34009415 73941). The randomization list will be created by La Roche sur Yon Clinical Research Unit and transmitted to the pharmacy department of Nantes University Hospital, which will prepare the blinded products. Numbered and identically labeled boxes with the study number will be produced. Each box will contain a 20-ml vial of the study drug (ropivacaine or placebo according to the randomization number). The syringe will be prepared in a specific room outside the delivery room by a midwife or an anesthetist not directly involved in patient management. A label “ROPISIO Study” and the randomization number will be located on the syringe without any information about the product (ropivacaine or placebo) inside. Then, the syringe will be given to the clinician who will be performing the suture of the episiotomy. Thus, the clinician and the mother will be blinded.

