### Statistical analysis

Both intention-to-treat and per-protocol analyses will be conducted, following the Consolidated Standards of Reporting Trials (CONSORT) guidelines for randomized controlled trials and will be conducted with the statistician and researchers blinded to group status. The two groups will be described for demographic characteristics and risk factors for perineal pain after episiotomy. The existence of a “ropivacaine effect” (i.e., a difference between the two groups for the primary outcome measure and the secondary outcome measures) will be analyzed. In case of missing data for the primary endpoint, two types of imputation will be realized (multiple imputation and worst case imputation): NPRS strictly superior to 3/10 on the perineal repair area. The percentage of patients with an NPRS strictly superior to 3/10 on the perineal repair area at D7 will be compared between groups (ropivacaine versus placebo) by a mixed effects logistic model in order to take into consideration parity, center, and group as fixed effects. A sensitivity analysis will be performed to consider analgesic administration at H2 and D7. The analgesic consumption will be added in a fixed effects model. A generalized linear mixed regression approach will be used for three criteria: the impact of perineal pain on sexuality (FSFI), depression (EPDS), and quality of life (SF-36) at D7, M3, and M6. This analysis allows taking into account intraindividual and interindividual variability. The group and temporal effects will thus be estimated.

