### Sample size

According to previous research [5, 8, 9], approximately 70% of patients experience perineal pain due to an episiotomy at D7 postpartum. To show a relative reduction of at least 30% in this incidence in the ropivacaine arm with 90% power at the 5% level of significance and a bilateral test, the study requires 124 women with episiotomy in each group. In order to ensure sufficient power in the event of participant dropout, an additional 10% will be recruited. Therefore, a total of 272 patients should be included in the study (136 in both groups).

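### Mode of delivery is fixed before randomisation and should be available for every woman, yet the primary day 7 model adjusts only for center and parity: an optional, small gain in precision

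*Protocol article*

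**What the plan says.** All references are to the Protocol article.

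- **Study population.** Inclusion criterion "3) spontaneous vaginal delivery or operative vaginal delivery" makes both modes of birth eligible.
- **Randomization.** "The randomization will be centralized and stratified by center and parity", in a 1:1 ratio. Allocation takes place between the episiotomy and its repair, when the mode of delivery is already settled.
- **Statistical analysis.** The primary comparison of the proportion with NPRS above 3 at day 7 uses a logistic model whose fixed effects are group, center and parity. A sensitivity analysis adds analgesic consumption. Other prognostic factors are handled descriptively: "The two groups will be described for demographic characteristics and risk factors for perineal pain after episiotomy".
- **Data management.** The eCRF has a file on the pregnancy, labor and delivery. Mode of delivery is not named as a field, but eligibility cannot be confirmed without it.
- **Background.** One cited study related chronic pain at 5 months to obstetric and postpartum factors. The only example given is pain in the first 48 hours.

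**The concern.** Mode of delivery is a plausible source of variation in perineal pain, it precedes treatment, and it should be in the data for every woman. Adjusting for such a variable cannot introduce bias through treatment. If the variable is prognostic, adjustment recovers some power and removes the effect of chance imbalance on the estimate.

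The plan leaves mode unadjusted. Its one further covariate, analgesic consumption in the sensitivity model, is measured after randomisation and could itself be affected by treatment. Mode of delivery is the safer choice.

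Two things are at stake: a little power, and a cleaner reading of the result if the baseline table shows more operative births in one arm. In that case an adjustment chosen after unblinding would be open to dispute, and a prespecified one would not.

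**Working it through.** **Step 1. Reproduce the plan's figure.** Sample size states a test "with 90% power at the 5% level of significance and a bilateral test" and says "the study requires 124 women with episiotomy in each group". The Abstract gives the rates as 70% and 50%.

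n = [z(0.975)·√(2·p̄·(1−p̄)) + z(0.90)·√(p1(1−p1) + p2(1−p2))]² / (p1−p2)², with p̄ = 0.60

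= [1.960·√0.48 + 1.2816·√0.46]² / 0.04 = (1.358 + 0.869)² / 0.04 ≈ 124 per arm.

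The figure reproduces. With the 10% allowance, 124 × 1.10 = 136.4, taken as 136, or 272 in total. The rates are averages over both modes of birth, so the sample size does not depend on adjusting for mode.

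**Step 2. Assumptions.** The article gives neither the share of operative births nor their effect on day 7 pain. Assumed: 30%, 50% or 70% operative, and an odds ratio of mode with NPRS above 3 at day 7 of 1, 1.5, 2 or 3.

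**Step 3. Power without and with mode.** Simulated logistic Wald test, 124 per arm, marginal rates held at 70% and 50%, 3,000 runs per cell. The model has group alone, then group plus mode.

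| Operative share | Odds ratio | Without | With | Gain (points) |
|---|---|---|---|---|
| 30% | 1 | 0.8823 | 0.8850 | 0.3 |
| 30% | 1.5 | 0.8937 | 0.8980 | 0.4 |
| 30% | 2 | 0.8980 | 0.9073 | 0.9 |
| 30% | 3 | 0.8960 | 0.9140 | 1.8 |
| 50% | 1 | 0.8973 | 0.8990 | 0.2 |
| 50% | 1.5 | 0.8973 | 0.9060 | 0.9 |
| 50% | 2 | 0.8857 | 0.8990 | 1.3 |
| 50% | 3 | 0.9027 | 0.9203 | 1.8 |
| 70% | 1 | 0.9013 | 0.9037 | 0.2 |
| 70% | 1.5 | 0.8897 | 0.8913 | 0.2 |
| 70% | 2 | 0.8927 | 0.9090 | 1.6 |
| 70% | 3 | 0.8960 | 0.9123 | 1.6 |

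The Monte Carlo standard error of each power is 0.5 to 0.6 points. The 0.2 to 0.3 points at an odds ratio of 1 are not a real gain, so the gain at 1.5 is close to nothing. A further simulation with center and parity already in the model, which is closer to the planned analysis, gave no loss at an odds ratio of 1 and gains of about 0.3 points at 1.5, 1 at 2 and 2 at 3.

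**Step 4. Type I error.** With 70% in both arms, rejection was 4.3 to 5.6% without mode and 4.6 to 5.7% with it (standard error about 0.4 points). Both are nominal.

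**Step 5. Chance imbalance.**

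- At 136 per arm and 40% operative, SD = √(2 × 0.4 × 0.6 / 136) = 0.059. The chance of a difference of 10 points or more between arms is about 9%.
- At 124 per arm and 50% operative, SD = √(2 × 0.25 / 124) = 0.0635, so the 95% range is ±12.4 points.
- With a placebo rate of 70% and 50% operative, an odds ratio of 2 means 62.8% with pain after spontaneous and 77.2% after operative birth, a gap of 14.3 points. An odds ratio of 3 means 58.9% and 81.1%, a gap of 22.2 points.
- An imbalance at the edge of the 95% range then shifts the crude risk difference by about 0.1245 × 14.3 = 1.8 points (odds ratio 2) or 0.1245 × 22.2 = 2.8 points (odds ratio 3), against a target of 20.

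**Step 6. Change in the odds ratio.** The marginal treatment odds ratio at 70% vs 50% is (0.5/0.5)/(0.7/0.3) = 0.429. Conditional on mode with 50% operative, the odds of pain after spontaneous birth are 1.690 on placebo and 1/√2 = 0.707 on ropivacaine when the mode odds ratio is 2, giving 0.707/1.690 = 0.418. When it is 3, they are 1.432 and 1/√3 = 0.577, giving 0.577/1.432 = 0.403.

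**The case against.** The strongest reply is that nothing here is wrong. The primary model adjusts for exactly the factors used in stratification. Leaving out one further covariate is a legitimate choice, and other obstetric variables could be proposed on the same grounds. That stands, and it is why the point is optional.

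A reader might infer that a known source of pain variation has been left uncontrolled. The article does not support this. It gives no pain rates by mode and never names mode as a predictor of day 7 pain. The Background statement concerns 5 months and unspecified factors. Randomisation balances mode in expectation, the planned test already allows for chance imbalance, and the type I error is nominal without the covariate. "Plausible" and "unadjusted" are as far as the text goes.

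A reader might also fault the stratification. Trial status reports that all 272 women have been included, so nothing can be changed there.

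It can further be said that extra covariates belong in a statistical analysis plan, which is not shown. This holds for supportive analyses. It holds less for the primary model, whose fixed effects the article states. If the analysis plan already adds mode of delivery to that model, the point is met.

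Finally, adjustment is not entirely free, because the odds ratio is non-collapsible. This is correct. Step 6 shows the change is small, and a standardised risk difference deals with it.

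**Conclusion.** The point holds as an optional gain in precision. Mode of delivery is a baseline variable that eligibility requires and that falls within the planned delivery data, and the stated primary model does not use it. The planned analysis remains valid, and the sample size is unaffected.

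The benefit is roughly 0.3 to 2 points of power for a mode odds ratio of 1.5 to 3, and nothing lost at 1. It also protects against a shift of 1.8 to 2.8 points in the risk difference under an imbalance at the edge of its 95% range (odds ratio 2 to 3). These sizes rest on assumed odds ratios and assumed shares of operative births, none of which is in the article. If mode is correlated with parity or center, the gain over the planned model would be smaller.

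**What to change.** Before unblinding:

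- add mode of delivery (spontaneous vs operative) as a prespecified fixed effect beside center and parity in the primary day 7 model;
- keep the center-plus-parity model as a supporting analysis;
- report a marginal (standardised) risk difference with the adjusted odds ratio, so that the result can be set against the 70% vs 50% design assumption;
- confirm that mode of delivery is a named eCRF field.

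The cost is a sentence or two in the analysis section and one extra model parameter. The adjusted odds ratio will differ slightly from one that does not condition on mode. Randomisation and sample size stay as they are, and no new data are needed as long as the field exists.
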